# Ultrasound-guided continuous parasacral ischial plane block for diabetic foot ulcer healing: study protocol for a single-centre, prospective, randomised, open-label, blinded-endpoint controlled trial

**DOI:** 10.3389/fendo.2026.1884667

**Published:** 2026-08-17

**Keywords:** diabetic foot ulcer, parasacral ischial plane block, regional anaesthesia, sympathetic blockade, wound healing

## Abstract

**Introduction:**

Diabetic foot ulcers (DFU) represent a significant global health burden, drastically reducing quality of life and increasing amputation risk. Associated pain and peripheral vascular disease complicate management and healing. Continuous parasacral ischial plane block (CPIPB), a regional anaesthesia technique targeting the sacral plexus, has shown potential in preclinical studies and feasibility assessments to improve lower limb analgesia and perfusion by modulating sympathetic tone. This trial aims to evaluate the efficacy and safety of CPIPB combined with standard of care (SOC) compared to SOC alone for promoting the healing of chronic DFU.

**Methods and analysis:**

This study utilizes a single-centre, prospective, randomised, open-label, blinded-endpoint (PROBE) parallel-group design. A total of 78 participants aged 20–89 years with a DFU (University of Texas Classification 1A-2D) present for >4 weeks but <1 year, with an area between 1–20 cm², and adequate perfusion (ABI >0.7 or equivalent) will be recruited after a 2-week SOC run-in period (inclusion requires <30% wound area reduction). Participants will be randomised (1:1) using variable block randomisation to either: 1) CPIPB + SOC: ultrasound-guided catheter placement in the parasacral ischial plane for continuous infusion of 0.2% ropivacaine at 5 mL/h for 14 days, combined with SOC; or 2) SOC alone: including glycaemic control, appropriate debridement, and standard dressings. The primary outcome is the incidence of complete ulcer healing at 12 weeks. Secondary outcomes include time to complete healing, percentage change in ulcer area, proportion achieving ≥50% area reduction, ulcer recurrence, infection rates, pain scores (VAS), lower limb perfusion assessments (TcPO2, Peak Systolic Velocity), health-related quality of life (Wound-QoL), and safety events. Statistical analysis will primarily use the intention-to-treat principle, comparing groups using chi-square tests, t-tests/Mann-Whitney U tests, Kaplan-Meier analysis, and logistic/linear regression models adjusting for baseline covariates where appropriate.

**Discussion:**

This study aims to evaluate the effects of a 12-week treatment with CPIPB and SOC on patients with DFU. We hypothesize that, compared to SOC alone, CPIPB combined with SOC would significantly improve ulcer healing without provoking significant adverse reactions. These findings potentially pave the way for a safe and effective adjunctive therapy for DFU.

**Clinical trial registration:**

https://www.chictr.org.cn/, identifier ChiCTR2400083504.

## Introduction

Chronic non-healing ulcers, particularly diabetic foot ulcers (DFU), pose a significant global health challenge. It is estimated that up to 15% of individuals with diabetes mellitus will develop a lower extremity ulcer during their lifetime, leading to a significant impairment of quality of life and a dramatic increase in the risk of lower limb amputation (1). DFU are among the most common and severe complications of diabetes, arising from a complex interplay of factors including peripheral neuropathy, peripheral artery disease (PAD), and infection (2). Effective DFU management necessitates comprehensive strategies aimed at promoting ulcer healing and reducing amputation risk (3).

Pain is a frequent symptom for patients with DFU, primarily stemming from diabetic peripheral neuropathy (DPN) and PAD (4). DPN, encompassing sensory, motor, and autonomic nerve damage, is a critical risk factor for ulceration due to loss of protective sensation (5, 6). Concurrently, PAD, characterized by reduced lower limb blood flow, tissue hypoxia, and insufficient nutrient supply, can cause claudication, rest pain, and impaired wound healing, potentially leading to critical limb ischaemia, ulceration, and gangrene (7). Lower limb pain profoundly affects patients’ mobility, increases fall risk, hinders wound healing, and contributes to psychological comorbidities such as anxiety and depression (8). Furthermore, pain is an independent predictor of amputation risk in DFU patients (9, 10). Therefore, pain management is an important component of the treatment process for patients with diabetic foot ulcers. It requires a comprehensive consideration of factors such as neuropathy, vascular disease, and infection, and appropriate therapeutic measures should be taken to alleviate pain, improve the patient’s quality of life, and reduce the risk of amputation (11, 12).

PAD, especially vascular stenosis, significantly influences DFU treatment and prognosis (13). Chronic hyperglycaemia damages vessel walls, leading to stenosis or occlusion and subsequent ischaemia, increasing ulcer risk and impairing healing (14). This is often characterized by diffuse, multi-vessel, infra-popliteal disease with long occlusions, poor collateralization, medial calcinosis, and vasoconstriction, complicating revascularization efforts and wound care (15, 16). Addressing lower limb ischaemia is thus a cornerstone of DFU management.

Regional anaesthesia techniques targeting the lower limb may offer benefits beyond analgesia by modulating sympathetic tone and improving perfusion. Ultrasound-guided continuous parasacral ischial plane block (CPIPB) is a novel technique for continuous sacral plexus blockade. Our prior research standardized the CPIPB catheter placement procedure, confirming its feasibility and safety (17). We observed that CPIPB provides effective lower limb analgesia and appears to improve circulation via vasodilation, likely through blockade of sacral plexus and sacral sympathetic nerves (18). Subsequent preclinical work suggested that CPIPB promotes wound angiogenesis following sympathetic blockade, thereby accelerating DFU healing (19).

Given these preliminary findings, this clinical trial aims to determine whether CPIPB, as an adjunct to standard of care (SOC), can clinically accelerate the healing of chronic, non-healing DFU compared to SOC alone. We will conduct a randomised parallel-controlled trial to determine the impact of CPIPB on patients with DFU. We hypothesize that CPIPB would significantly improve ulcer healing without provoking significant adverse reactions compared to SOC. In addition, these findings potentially pave the way for a safe and effective adjunctive therapy for DFU.

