#### Sample size

Based on previous research, the healing rate in the SOC group is approximately 47% (21). Our institutional pre-experiment (pilot study) of DFU patients receiving continuous regional block showed that approximately 80% of participants achieved complete wound closure within 12 weeks; thus, we hypothesized that CPIPB + SOC will increase the 12-week healing rate to approximately 80%. To detect this difference with 90% power (β=0.10) at a one-sided significance level of α=0.05, 35 participants are required per group. Accounting for an estimated 10% dropout rate, a total of 78 participants (39 per group) will be recruited.

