#### Secondary outcomes

Secondary end points included wound area reduction, 12-month incidence of both recurrence and complete healing, lower limb haemodynamic assessments, incidence of amputation,pain assessment, Wound-QoL assessment, and adverse events.

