#### Secondary outcome analysis

Time-to-event outcomes (time to healing, time to recurrence) will be analysed using Kaplan-Meier curves and compared using the log-rank test. Hazard ratios (HR) with 95% CIs will be estimated using Cox proportional hazards regression, adjusting for covariates.

Continuous outcomes (e.g., percentage area reduction, change in VAS, change in TcPO2, Wound-QoL scores) will be compared using independent t-tests or Mann-Whitney U tests, depending on data distribution. Analysis of covariance (ANCOVA) may be used to adjust for baseline values.

Binary secondary outcomes (e.g., proportion achieving ≥50% area reduction, infection incidence) will be compared using chi-square or Fisher’s exact tests, with ORs and 95% CIs from logistic regression.

Adverse event rates will be summarized descriptively and compared using Fisher’s exact test.

To address missing primary and secondary outcome data, multiple imputation by chained equations (MICE) will be performed as a sensitivity analysis under the missing-at-random (MAR) assumption. No interim analysis is planned for this study due to the relatively modest sample size (n=78). To control the family-wise error rate, the Bonferroni correction will be applied to adjust p-values for multiple comparisons among secondary outcomes. All statistical tests will be two-sided with a significance level set at P < 0.05. Statistical analysis will be performed using SPSS version 18.0 (SPSS, Inc., USA) and GraphPad Prism version 8.2.

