Should this trial demonstrate the superiority of CPIPB plus SOC over SOC alone, the clinical implications would be substantial. This technique could offer a novel, safe, and effective adjunctive therapy for a challenging patient population that currently has limited options. By targeting key pathophysiological drivers of non-healing ulcers, CPIPB could potentially accelerate healing times, reduce the incidence of complications like severe infections, and ultimately lower the rate of major amputations. The findings will also pave the way for future research. Larger, multicentre trials will be necessary to confirm our results and establish the generalizability of the technique. Subsequent studies could explore the optimization of the CPIPB protocol, including the ideal duration of infusion and concentration of local anaesthetic. Furthermore, investigating the efficacy of CPIPB in specific subgroups of DFU patients, such as those with severe ischemic pain who are not candidates for revascularization, would be a valuable next step. In conclusion, this study protocol outlines a trial for a mechanistically targeted therapy that has the potential to significantly improve clinical outcomes and quality of life for patients suffering from the devastating consequences of diabetic foot ulcers.

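### The hypothesis includes absence of harm relative to SOC, but no safety criterion is stated and the only planned comparison, a Fisher test in 39 per arm, cannot support it

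*Protocol article*

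**What the plan says.** The Introduction gives a two-part hypothesis: "We hypothesize that CPIPB would significantly improve ulcer healing without provoking significant adverse reactions compared to SOC". The Discussion paragraph of the abstract has the same two parts.

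Under Secondary outcome analysis, the comparative plan for safety is one sentence: "Adverse event rates will be summarized descriptively and compared using Fisher’s exact test". The general rule in that section is "All statistical tests will be two-sided with a significance level set at P < 0.05", and for multiplicity "the Bonferroni correction will be applied to adjust p-values for multiple comparisons among secondary outcomes". The Secondary outcomes section ends its list with "pain assessment, Wound-QoL assessment, and adverse events", so harms belong to the set that Bonferroni covers, and no exemption is stated.

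The Sample size section uses healing rates only and concludes: "Accounting for an estimated 10% dropout rate, a total of 78 participants (39 per group) will be recruited". Study design calls the trial a superiority trial. No section states a safety margin, an acceptable complication rate or a confidence-interval criterion.

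The Discussion says that, if superiority is shown, "This technique could offer a novel, safe, and effective adjunctive therapy for a challenging patient population that currently has limited options".

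**The concern.** A difference test can give evidence that harm exists. It cannot give evidence that harm is absent unless the trial is large enough to exclude a stated amount of it. Here the hypothesis claims absence, the planned test looks for presence, and no amount is stated.

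The word significant in the hypothesis does not settle the matter. If it means statistically significant, the clause holds whenever a small trial fails to reject. If it means clinically significant, no threshold is given. On either reading the clause cannot be evaluated as written.

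The harms most specific to the intervention make the comparison weaker still. Catheter-site infection, catheter dislocation and local anaesthetic systemic toxicity, all named under Harms, need a catheter or an infusion. The SOC arm has neither and will contribute no such events. The informative quantity is the incidence in the CPIPB arm with its interval, not a p-value against an arm that cannot have the event.

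At stake is the safety conclusion for a 14-day indwelling catheter, with part of the monitoring at home, in a trial whose Discussion already links the word safe to a positive healing result.

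**Working it through.** **Inputs.** 39 per group recruited; 35 per group before dropout; healing 47% v 80%; 90% power; one-sided α=0.05 (Sample size). Tests two-sided at 0.05, Fisher for adverse events, Bonferroni among secondary outcomes (Secondary outcome analysis). Assumed here, because the article does not give them: the true complication rates, and a Bonferroni family of 7 to 10 comparisons.

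**1. The plan's own figure.** Pooled two-proportion formula, no continuity correction, mean rate 0.635:

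n = [1.645·√(2·0.635·0.365) + 1.282·√(0.47·0.53 + 0.80·0.20)]² / 0.33² = (1.120 + 0.820)² / 0.1089 ≈ 34.6, so 35 per group.

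35/0.9 = 38.9, so 39 per group and 78 in total. The stated size reproduces, and no safety quantity enters it.

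**2. What Fisher's test can detect against zero SOC events.** With k events on CPIPB and none on SOC in equal arms of 39, the two-sided p-value is 2·C(39,k)/C(78,k).

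| CPIPB v SOC | CPIPB rate | p |
|---|---|---|
| 4 v 0 | 10.3% | 0.1153 |
| 5 v 0 | 12.8% | 0.0545 |
| 6 v 0 | 15.4% | 0.0254 |
| 7 v 0 | 17.9% | 0.0116 |
| 8 v 0 | 20.5% | 0.0052 |
| 9 v 0 | 23.1% | 0.0023 |

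For k=5: 2 × 575,757 / 21,111,090 = 0.0545. So 5 v 0 is not significant and 6 v 0 is. With 35 per arm, 5 v 0 (14.3%) gives p=0.0536.

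Zero SOC events is the easiest case for detection. With one SOC event, 7 v 1 (17.9% v 2.6%) is still non-significant (p=0.056).

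**3. Power at assumed true rates.** With a SOC rate of zero, power is P(X ≥ 6) for X ~ Binomial(39, π):

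| True CPIPB rate π | Power |
|---|---|
| 10% | 19% |
| 13% | 40% |
| 15% | 54% |
| 20% | 82% |

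A true 13% v 0% is therefore missed about 60% of the time. When SOC also has events, power is lower: 17% for 15% v 5%, and 40% for 20% v 5%.

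**4. If Bonferroni covers adverse events.** The threshold is 0.05/7 = 0.0071 for 7 comparisons and 0.05/10 = 0.0050 for 10. From the table, 7 v 0 (0.0116) fails throughout this range. 8 v 0 (0.0052) passes for 7 to 9 comparisons (0.05/9 = 0.0056) and just fails at 10, where 9 v 0 is needed. Power against a true 13% falls to P(X ≥ 8) = 13%, or P(X ≥ 9) = 6%.

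**5. What the data could show by estimation.** With 0 of 39, the exact 95% upper limit is 1 − 0.025^(1/39) = 9.0%. With 5 of 39, the exact 95% interval is 4.3% to 27.4%, and the Newcombe interval for the difference from 0 of 39 is about 1.3 to 26.7 percentage points. Thus in the case where Fisher gives p=0.0545, estimation shows that a rate above one in four is not excluded.

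**The case against.** A reader might infer that the plan tests safety by non-significance and would pass a 13% complication rate as safe. The article does not say so. No section makes p ≥ 0.05 the criterion for safety, and the Fisher sentence does not refer back to the hypothesis. The word significant may be meant clinically.

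Safety reporting is also more than a p-value. A descriptive summary comes first, block-related complications are collected as a separate item under Follow-up data, and under Harms every adverse event is assessed for severity and causality. A 13% complication rate would be visible in that summary. The Discussion says only that the technique could offer a safe therapy, and it calls for larger multicentre trials.

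Three further limits stand. The SOC zero is structural only for events that need a catheter or infusion. Hypotension as defined under Hemodynamic safety monitoring can occur on SOC, and for serious adverse events a between-arm comparison is meaningful. Power is not poor everywhere: it reaches 82% at a true 20% v 0%. And the Bonferroni figures rest on an assumed number of comparisons.

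It can also be said that sizing on efficacy and adding a Fisher test for harms is common, and that interval methods are often left to an analysis plan. That is fair for the choice of interval. It does not answer the point, which concerns what the article states: a comparative no-harm hypothesis with no criterion, and a multiplicity rule that takes in harms as worded.

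**Conclusion.** The point holds in a limited form. The no-harm clause has no stated criterion, and the one comparative analysis planned for it cannot support it: 5 v 0 in 39 per arm is non-significant, a true 13% v 0% is missed about 60% of the time, and no events at all would still leave rates up to 9.0% within the exact 95% interval. As worded, the Bonferroni rule also makes harm harder to declare, needing 8 or 9 v 0 (20.5% or 23.1%).

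These figures assume full data on 39 per arm and no SOC events of the type in question. The Bonferroni figures further assume 7 to 10 comparisons including adverse events. The finding does not depend on the authors intending to read non-significance as safety. It should be corrected before analysis, but it leaves the primary analysis and the sample size untouched.

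**What to change.** - Restate the safety part of the hypothesis as an estimation objective, without the claim of no significant adverse reactions compared to SOC.
- Report catheter- and block-related complications in the CPIPB group as incidences with exact 95% confidence intervals.
- Report the between-arm risk difference for serious adverse events with its 95% interval.
- Exclude adverse events from the Bonferroni adjustment.
- State that a non-significant Fisher test will not be read as evidence of safety.
- In the Discussion, do not attach the word safe to a finding of superiority on healing.

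The cost is wording in the hypothesis, statistical methods and Discussion. No patients or data are added. The downside for the authors is a less favourable safety statement, since the intervals will be wide.

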## Methods and analysis

### Study design

This is a single-centre, prospective, randomised, open-label, blinded-endpoint (PROBE), parallel-group, controlled superiority trial. The PROBE design was specifically chosen to overcome the practical limitations of blinding patients and clinicians to the regional anaesthesia intervention, while ensuring rigorous, unbiased evaluation of the primary and secondary outcomes by blinded independent assessors. This study is conducted at Fuzhou University Affiliated Provincial Hospital in Fuzhou, China. This study will follow the Consolidated Standards of Reporting Trials (SPIRIT) guidelines (20). The study flowchart is shown in **Figure 1**.

**Figure 1 f1:**
[figure not shown]
Trial flow chart.

### Study setting

The recruitment and follow-up will be conducted at the wound care outpatient clinics of Fuzhou University Affiliated Provincial Hospital by a multidisciplinary staff consisting of anaesthesiologist, wound care nurses, podiatrists and plastic surgeons. The staff will screen patients at the respective outpatient clinics according to the following eligibility criteria: Potential participants will undergo a 2-week run-in period receiving SOC. Those whose target ulcer area reduction is less than 30% after this period will be eligible for randomisation if they meet all inclusion and none of the exclusion criteria.

**Inclusion criteria:**

Males and females aged between 20 and 89 yearsDocumented diagnosis of type 1 or 2 diabetesFoot ulcer at or below ankle with duration >4 weeks to <1 year■ If the index ulcer is post amputation, date of surgery must be >30days■ If>1ulcer is present, largest is considered as the study index ulcer■ Index ulcer must be ≥1cm from any other ulcers present on the footUlcer size ≥1 and ≤20 cm^2^ after debridement at start of run-in periodUlcer of UTC grade 1A, 1B, 1C, 1D, 2A, 2B, 2C, or 2DABI >0.7 with a TcPO_2_,>30 mmHg, skin perfusion >30 mmHg, toe pressure >30 mmHg, or Duplex ultrasound with biphasic waveforms below the kneeNo planned revascularization procedure or vascular surgery within the last or next 30 daysSubject and caregiver willing and able to comply with all specified care and visit requirementsSubject has a reasonable expectation of completing the studySubject completed 2-week run-in period with <30% wound size reduction

**Exclusion criteria:**

Evidence of gangrene on any part of affected limbDocumented evidence of osteomyelitis on any part of affected limbIndex ulcer has exposed boneActive Charcot foot on the study limbUncontrolled diabetes: HbA_1c_>12% (108 mmol/mol)Renal dialysis or creatinine >2.5 mg/dL (221 μmol/L)Known immune insufficiencyActive treatment for malignancy (not specific to study limb)Chronic steroid use or immunosuppressive agents within the last 3 months or anticipated to require them during the duration of the studySubject participated in another investigational device, drug, or biological trial within last 30 daysIndex ulcer exhibits signs of severe clinical infection that requires hospitalization or immediate surgical interventionSubject is pregnant at the time of screeningSubject has had a deep vein thrombosis within the last 30 daysSubject has received growth factor therapy, autologous platelet-rich plasma gel, bilayered cell therapy, dermal substitute, extracellular matrix, etc., within the screening periodLocal anaesthetic allergy

**Withdrawal criteria:**

Occurrence of a serious adverse event (SAE) or complication rendering continuation inappropriate;Participant’s voluntary withdrawal (withdrawal of consent);Loss to follow-up;Significant protocol deviation impacting the ability to assess efficacy or safety; investigator’s decision that withdrawal is in the participant’s best interest.

### Handling of dropout cases

Participants who discontinue early or are lost to follow-up will be contacted for a final assessment whenever feasible. Every effort will be made to collect efficacy and safety data for these individuals. The reasons for withdrawal will be recorded in both the case report form and the trial conclusion form.

### Random allocation and blinding

#### Blinding

This is an open-label study. Participants, clinicians administering the intervention, and personnel assessing most clinical outcomes are aware of the treatment allocation. For specific objective measurements, such as ulcer area assessment, hemodynamic readings, or laboratory analyses, outcome assessors remain blinded, and statisticians conducting the final analysis also remain blinded until the analysis is complete.

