### Outcomes

#### Primary outcome

The primary study end point was the percentage of ulcers in each group achieving 100% healing at 12 weeks. Complete healing is defined as 100% re-epithelialization without drainage or dressing requirements, confirmed at two consecutive visits 2 weeks apart by an independent, blinded wound specialist. To ensure objective evaluation, wound areas will be traced and verified using computerized planimetry (ImageJ) on standardized digital photographs (taken with fixed distance, positioning, and illumination). These photographs will be securely archived and cross-checked by a central, blinded adjudication committee of two senior plastic surgeons.

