## Limitations

Several limitations of this study protocol should be acknowledged. First, this is a single-centre trial conducted at a provincial hospital, which may limit the external validity and generalizability of our findings to other healthcare settings with different patient demographics. Second, although we have implemented a rigorous PROBE design and blinded independent outcome assessors to minimize detection bias, the open-label nature of the intervention may still theoretically introduce some performance bias. Third, the 14-day continuous CPIPB infusion is relatively short compared to the 12-week wound healing observation window, though it is designed to cross the critical early window of microvascular recovery and angiogenesis. Finally, the inclusion requirement of a 2-week run-in period with <30% wound area reduction may slightly restrict the representativeness of our randomized cohort to the broader diabetic foot ulcer (DFU) population by excluding acute, highly responsive, or rapidly healing wounds. Nevertheless, this run-in design significantly enhances the internal validity of the trial by focusing specifically on hard-to-heal, truly chronic ulcers that are most in need of advanced adjunctive therapies, thereby ensuring a more stringent and clinically meaningful evaluation of the efficacy of CPIPB.

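### The Study design section claims blinded assessment of the primary and secondary outcomes, but the Blinding section denies it for most clinical outcomes; the secondary and safety outcomes are the ones left without stated protection

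*Protocol article*

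**What the plan says.** Four places in the protocol article bear on this.

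- **Study design** gives the reason for choosing PROBE: patients and clinicians cannot practicably be blinded, so the design relies on "unbiased evaluation of the primary and secondary outcomes by blinded independent assessors".
- **Blinding** calls the study open-label. Participants and treating clinicians know the arm, and "personnel assessing most clinical outcomes are aware of the treatment allocation". The exception is narrower than the Study design claim: "For specific objective measurements, such as ulcer area assessment, hemodynamic readings, or laboratory analyses, outcome assessors remain blinded". It adds that "statisticians conducting the final analysis also remain blinded until the analysis is complete".
- **Primary outcome** is specific to complete healing. It is "confirmed at two consecutive visits 2 weeks apart by an independent, blinded wound specialist", and the archived photographs are "cross-checked by a central, blinded adjudication committee of two senior plastic surgeons".
- **Limitations** relies on "blinded independent outcome assessors to minimize detection bias" and then concedes only a possible performance bias from the open-label design.

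The outcomes beyond the primary one are listed in the Abstract, Secondary outcomes and Secondary outcome analysis. They cover area reduction, time to healing, 12-month healing and recurrence, infection, haemodynamics, amputation, pain (VAS), Wound-QoL and adverse events.

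**The concern.** Study design and Blinding cannot both be true of the secondary outcomes. Staff who work from the Blinding section and readers who rely on Study design would describe different trials.

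The stake is detection bias. The control arm receives standard care alone, with no sham catheter. An assessor who knows the arm and expects the block to work could lean in its favour when deciding whether a closed ulcer has recurred or whether a foot is infected. For adverse events the direction is less clear, because catheter-site inspection under Harms also means closer observation of the block arm. These outcomes are compared formally between arms. Secondary outcome analysis plans a log-rank test and Cox model for recurrence, chi-square or Fisher's exact tests with odds ratios for infection and other binary outcomes, and Fisher's exact test for adverse events. If the text stays as it is, the results could be reported as having blinded-endpoint protection that the Blinding section says they lack.

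**Working it through.** No arithmetic applies. The check sets each outcome against the assessor that the article states for it.

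| Outcome | Assessor stated | Status |
|---|---|---|
| Complete healing, 12 weeks | Blinded specialist plus blinded two-surgeon committee (Primary outcome) | Blinded, explicit |
| Complete healing, 12 months; time to healing | None separately; the Primary outcome definition plausibly carries over | Probably blinded, not confirmed |
| Area reduction, including the ≥50% responder outcome | Blinded (Blinding) | Blinded |
| Haemodynamics | Blinded (Blinding) | Blinded |
| Recurrence | None | Not stated; falls under the general rule in Blinding |
| Infection | None | As above |
| Amputation | None | As above |
| Adverse events | None | As above |
| Pain VAS, Wound-QoL | Questionnaires (Methods) answered by participants who know their arm (Blinding) | Open-label by nature |

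Step 1. Study design makes a claim about primary and secondary outcomes together and names no exception.

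Step 2. Blinding sets the opposite default. Assessors of most clinical outcomes are aware, and blinding is kept for specific objective measurements. Its list is introduced as examples, so an outcome missing from it is not thereby shown to be unblinded. Even so, recurrence and infection calls and the recording of adverse events are clinical judgements, and they do not fit naturally under objective measurements.

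Step 3. For complete healing, the more specific text under Primary outcome settles the matter. The Blinding section does not repeat it. Area tracing alone would not cover it, because the definition also requires a dry wound that needs no dressing. A cross-reference is missing, but the protection is stated.

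Step 4. For recurrence, infection, amputation and adverse events, no section supplies a blinded assessor that would override the default in Blinding. The Study design claim is unsupported there.

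Step 5. For VAS and Wound-QoL, a blinded person handing out the form would not help, because the respondent knows the allocation. The Study design claim cannot hold for these in any practical sense.

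Step 6. Limitations names detection bias as the thing that blinded assessors minimise and does not say for which outcomes. Read beside Blinding, it leaves out a limitation that the article itself creates.

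**The case against.** The strongest reply is that the endpoint that matters most is well protected. Complete healing, on which the trial is sized, has a blinded specialist and blinded adjudication of standardised photographs. Area, haemodynamic and laboratory assessors are blinded, and so are the statisticians. This stands. A reader might infer from the Blinding section that the PROBE protection is absent altogether, or that the primary outcome is assessed open-label. The documents do not support either reading.

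Two further replies also stand. First, the list in Blinding is illustrative, and 12-month healing plausibly inherits the blinded definition, so a count of blinded against unblinded secondary outcomes taken from that list would not be reliable. Second, Limitations does not mention secondary outcomes. A reader might take it as repeating the Study design claim in full, but its fault is only that it leaves the limit unsaid.

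It can also be said that extending blinded adjudication is a design preference when the error is one of wording. This stands in part. Infection is diagnosed from clinical signs under the guideline cited in the standard-care section, and photographs alone may not show these, so blinded adjudication of infection is debatable and is not asked for here. Amputation is hard to misrecord, although the decision to amputate is made in the open. Recurrence of an open wound is different. It can be judged from photographs by people already appointed, at little cost.

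None of this removes the contradiction between Study design and Blinding.

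**Conclusion.** The point holds as a contradiction with a limited reach. Study design overstates blinding relative to the Blinding section. The overstatement affects infection, recurrence, amputation and adverse events, which have no stated blinded assessor, and VAS and Wound-QoL, which unblinded participants report. Limitations should acknowledge this and does not.

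It should be corrected, but it does not threaten the primary comparison, because the Primary outcome section provides explicit blinded assessment.

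No numerical size can be given. A reader might put a figure on it by supposing that some percentage of infection or recurrence calls differ by arm, but the resulting bias would only restate that supposition, and nothing in the documents supports a range. The sample size is unaffected.

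The conclusion assumes that the specific text under Primary outcome governs complete healing wherever the Blinding section is silent.

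**What to change.** 1. Rewrite the Blinding section to state, outcome by outcome, who assesses it and whether that person is blinded. Confirm there that complete healing, at 12 weeks and at 12 months, is assessed blind in line with the Primary outcome section.
2. Have the already appointed blinded wound specialist and two-surgeon committee also judge ulcer recurrence from standardised photographs, including at the 1-year visit.
3. Declare VAS, Wound-QoL, adverse events and any other outcome not assessed in this way (including infection and amputation, if they stay with unblinded staff) as open-label.
4. Narrow the Study design claim to the outcomes that are truly blinded. In Limitations, restrict the detection-bias statement to the same outcomes and acknowledge that detection bias remains possible for the others.

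Items 1, 3 and 4 are wording only. Item 2 costs extra photographs and some work to mask them. No change to the sample size or the statistical methods is needed.
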